#### **6.8.5 Visit 8: Day 7**

The subject will return to the clinic 7 days after vaccination, where the following assessments will be completed:

- Collect the stool sample that the subject has brought to clinic for culture of vaccine strain *S. typhi* (Ty2 *aroC* *ssaV*) ZH9
- Determine and record vital signs (blood pressure, temperature and pulse)
- Review Diary Cards and summarise data in CRF.
- Enquire about and record any adverse events since the last visit (see Section 6.8.9) to include an examination for any signs of splenomegaly
- Enquire about and record any changes in concomitant medication since the last visit
- Draw blood for:
  - Serum biochemistry and haematology
  - Serum IgA (ELISA assay)
  - Determining the number of ASC secreting IgA (ELISPOT assay; only for subjects aged at least 11 years and weighing at least 27 kg)
- Obtain urine sample for:
  - Dipstick test, and if the dipstick is positive for leucocyte esterase and nitrites, a separate sample will be sent for microscopy, culture and sensitivity and also to determine if vaccine strain *S. typhi* (Ty2 *aroC* *ssaV*) ZH9 is present
- Make an appointment for Study Day 8 and instruct the subject to bring a stool sample to the visit

#### **6.8.6 Visit 9, 10, 11, 12, 13 and 14: Days 8, 9, 10, 11, 12 and 13**

The subject will return to the clinic where the following assessments will be completed:

- Collect the stool sample that the subject has brought to clinic for culture of vaccine strain *S. typhi* (Ty2 *aroC* *ssaV*) ZH9
- Determine and record vital signs (blood pressure, temperature and pulse)
- Review Diary Cards and summarise data in CRF.

- Enquire about and record any adverse events since the last visit (see Section 6.8.9) to include an examination for any signs of splenomegaly
- Enquire about and record any changes in concomitant medication since the last visit
- Make an appointment for a clinic visit on the following day and instruct the subject to bring a stool sample to the visit

#### **6.8.7 Visit 15: Day 14**

The subject will return to the clinic 14 days after dosing, when the following assessments will be completed:

- Collect the stool sample that the subject has brought to clinic for culture of vaccine strain *S. typhi* (Ty2 *aroC* *ssaV*) ZH9
- Determine and record vital signs (blood pressure, temperature and pulse)
- Review Diary Cards and summarise data in CRF
- Enquire about and record any adverse events since the last visit (see Section 6.8.9) to include an examination for any signs of splenomegaly
- Enquire about and record any changes in concomitant medication since the last visit
- Draw blood for:
  - Serum biochemistry and haematology
  - Serum IgG (ELISA assay)
  - Serum IgA (ELISA assay)
- Obtain urine sample for:
  - Dipstick test, and if the dipstick is positive for leucocyte esterase and nitrites, a separate sample will be sent for microscopy, culture and sensitivity, and also to determine if vaccine strain *S. typhi* (Ty2 *aroC* *ssaV*) ZH9 is present
- Make an appointment for Study Day 28.

#### **6.8.8 Visit 16: Day 28**

The subject will return to the clinic 28 days after dosing, where the following assessments will be completed:

- Physical examination including vital signs (blood pressure, temperature and pulse)
- Enquire about and record any adverse events since the last visit (see Section 6.8.9) to include an examination for any signs of splenomegaly
- Enquire about and record any changes in concomitant medication since the last visit
- Draw blood for:
  - Serum biochemistry and haematology
  - Serum IgG (ELISA assay)

- Obtain urine sample for:
  - Pregnancy test (females of 11 years and older only)
  - Dipstick test, and if the dipstick is positive for leucocyte esterase and nitrites, a separate sample will be sent for microscopy, culture and sensitivity, and also to determine if vaccine strain *S. typhi* (Ty2 *aroC* *ssaV*) ZH9 is present

#### **6.8.9 Specific Safety Reviews at Each Visit**

Visits to the clinic are scheduled daily, for the first 14 days post-dosing. At these visits, the study staff will obtain and record the subject's blood pressure, oral body temperature, pulse and assess for signs of splenomegaly. The Investigator will enquire of the subject, and the parents or guardians, as to whether the subject has had any signs or symptoms of typhoid fever. Specifically, enquiries will relate to whether the subject has had any of the following;

- Temperature of 38.5°C or above.
- Flushed face
- Hot, dry skin
- Low output of urine and/or dark urine
- Loss of interest in eating
- Constipation or diarrhoea
- Vomiting
- Headache
- Aching all over
- Nausea
- Chills
- Abdominal pains, cramps or discomfort

#### **6.8.10 Unscheduled Visits**

In addition to the scheduled visits described above, the subjects' oral body temperature will be taken at home, twice daily. If a subject shows sustained signs and symptoms of a clinical infection defined as a confirmed fever of = 38.5°C, or other signs and symptoms as outlined above, they will be instructed to make additional unscheduled visits to the clinic. At such visits the subject will be assessed and biological samples taken for culture if clinically indicated. If a clear diagnosis can be made, as in the case of Dengue fever, the subject will be managed accordingly. Should a confirmed fever of = 39.0°C be recorded twice over a 48-hour period, or a severe fever of = 39.5°C ever be recorded, blood sample for cultures will be taken to investigate if *S. typhi* (Ty2 *aroC* *ssaV*) ZH9 is present in the blood.

## **7 IMMUNOGENICITY, SAFETY AND LABORATORY ASSESSMENTS**

### **7.1 Assessments of Immunogenicity**

Full details of the immunogenicity assays including sample collection, processing, storage and analysis are provided in the Laboratory Manual. ELISPOT assays will be conducted at the study centre, ELISA samples for assay will be shipped to Emergent Product Development UK Ltd after preparation and freezing, under the supervision of [name] the Principal Investigator for this study and in accordance with the instructions provided by Emergent Product Development UK Ltd.

#### **7.1.1 Measure of Antibody Secreting Cells by ELISPOT**

ELISPOT assay of the number of ASCs secreting IgA to LPS will be conducted on blood samples taken on Days 0 and 7 for subjects aged at least 11 years and weighing at least 27kg. The assay will be undertaken within 24 hours of the sample being taken.

Human PBMCs will be separated from whole blood by density gradient centrifugation. After centrifugation the lymphocytes will be collected and washed. The cells will then be suspended in culture medium and different dilutions added to microtitre wells coated with *S. typhi* LPS. Following overnight incubation, the cells will be removed. Zones of antigen-specific secreted IgA antibody bound to the plate will be visualised by the addition of alkaline phosphatase-labelled anti-human IgA antibodies followed by the addition of 5-bromo-4-chloro-3-indolyl-phosphate (BCIP)/Nitro Blue Tetrazolium (NBT) substrate. Regions of specific antibody appear as blue ELISPOTS, and these will be observed and counted using an inverted microscope and then photographed. The number of ASC/10^6 cells can then be calculated from the results obtained with different dilutions of PBMCs.

#### **7.1.2 Analysis of LPS Specific Immunoglobulin G by the ELISA Assay**

Serum for ELISA assays for IgG will be frozen immediately after collection on Days 0, 14 and 28, and shipped to Emergent Product Development UK Ltd for analysis after all subjects have completed 28 days for LPS-specific IgG serum antibody.

Microtitre plates are coated with *S. typhi* LPS and blocked with a non-specific protein to mask unbound binding sites. Human serum samples are added to the wells and any antibodies present that are specific for the *S. typhi* LPS will bind to the coated plate. These bound antibodies are then detected using a double antibody system. First, an unlabelled anti-human IgG antibody is added which, in turn, is detected by a horseradish peroxidase (HRP)-labelled conjugate which causes a detectable colour change when 3,3',5,5'-Tetramethylbenzidine (TMB) substrate is added. The products are quantified with an automated ELISA reader at 450 nm and the concentration of anti-LPS human IgG is determined by extrapolation of the dilution that is within the range of the standard curve.

### **7.1.3 Analysis of LPS Specific Immunoglobulin A by the ELISA Assay**

Serum for ELISA assays for IgA will be frozen immediately after collection on Days 0, 7 and 14 and shipped to Emergent Product Development UK Ltd for analysis after all subjects have completed 14 days for LPS-specific IgA serum antibody.

Microtitre plates are coated with *S. typhi* LPS and blocked with a non-specific protein to mask unbound binding sites. Human serum samples are added to the wells and any antibodies present that are specific for the *S. typhi* LPS will bind to the coated plate. These bound antibodies are then detected using a double antibody system. First, an unlabelled anti-human IgA antibody is added which, in turn, is detected by a horseradish peroxidase (HRP)-labelled conjugate which causes a detectable colour change when 3,3',5,5'-Tetramethylbenzidine (TMB) substrate is added. The products are quantified with an automated ELISA reader at 450 nm and the concentration of anti-LPS human IgA is determined by extrapolation of the dilution that is within the range of the standard curve.

## **7.2 Assessment for Safety**

### **7.2.1 Laboratory Tests**

Subjects will be asked to attend the clinic every day for the first 14 days of the study. At these visits the Investigator (a paediatrician) will obtain and record the subject's blood pressure, oral body temperature, pulse and assess for signs of splenomegaly. The Investigator will enquire of the subject, and the parents or guardians, as to whether the subject has had any signs or symptoms of typhoid fever. Specifically, enquiries will relate to whether the subject has had any of the following;

- Temperature of 38.5°C or above
- Flushed face
- Hot, dry skin
- Low output of urine and/or dark urine
- Loss of interest in eating
- Constipation or diarrhoea
- Vomiting
- Headache
- Aching all over
- Nausea
- Chills
- Abdominal pains, cramps or discomfort

Based on the examination and the responses to the questioning, the Investigator will initiate appropriate investigations, including biological samples for culture, to determine if the child has an infection and the cause of the infection.

The faecal shedding pattern of the bacterial strain has been determined in adults with no subject, to date, shedding the vaccine strain for more than 7 days after dosing. The faecal shedding pattern in children is expected to be the same but this study will investigate whether paediatric subjects shed for a shorter or longer period than adults.

The following tests will be performed on blood samples collected at screening and Days 0, 7, 14 and 28:

**Biochemistry:**

Sodium, potassium, chloride, creatinine, blood urea, aspartate aminotransferase (AST), alanine aminotransferase (ALT), alkaline phosphatase, total bilirubin, gamma-glutamyl transferase (gGT), serum amylase, total protein and albumin.

**Haematology:**

Haemoglobin, haematocrit, red blood cell count, white blood cell count (total and differential), platelet count.

In total, approximately 27.5 mL of blood will be taken from each subject, **aged 5 to 10 years** and weighing more than 17 kg, for the immunogenicity and safety tests during the 28-day phase of the study. The maximum amount taken will be no more than 5.5mL at any one visit.

In total, approximately 43.5 mL of blood will be taken from each subject, **aged 11-14 years** and weighing more than 27 kg, for the immunogenicity and safety tests during the 28-day phase of the study. . The maximum amount of blood taken will be no more than 13.5 mL at any one visit.

If a subject shows sustained signs and symptoms of a clinical infection, defined as a confirmed fever of  $\geq 38.5^{\circ}\text{C}$ , they will be instructed to make additional unscheduled visits to the clinic. At such visits the subject will be assessed and biological samples taken for culture if clinically indicated. Should a confirmed fever of  $\geq 39.0^{\circ}\text{C}$  be recorded twice over a 48-hour period, or a severe fever of  $\geq 39.5^{\circ}\text{C}$  ever be recorded, blood cultures will be taken to investigate if *S. typhi* (Ty2 *aroC* *ssaV*) ZH9 is present in the blood. Each blood culture would require a blood draw of 1-3 mL.

Urine samples will be tested, by dipstick, at screening and Days 0, 7, 14 and 28 for the presence of nitrites and leucocyte esterase. If the dipstick is positive for nitrites and leucocyte esterase a sample will be sent for culture and sensitivity.

Stool samples will be collected for culture at all visits except Day 28. Details of the assay method will be documented in the Laboratory Manual.

Any post vaccination unformed/loose stool experienced by the subject will be recorded as an adverse event.

**7.2.2 Physical Examination**

A standard physical examination will be performed at the Screening visit and at Day 28. Any abnormalities will be described in the CRF. This will include assessments of the following:

- Cardiovascular system
- Respiratory system
- Nervous system

- Skin and appendages
- Abdominal/gastrointestinal system
- Musculoskeletal system
- Ear, nose and throat

### **7.2.3 Vital Signs**

Vital signs will be determined and recorded at each study visit and recorded on the CRF. Vital signs include:

- Sitting (5 minute) systolic and diastolic blood pressure
- Oral temperature (see also section 7.2.4)
- Pulse rate

### **7.2.4 Diary Card**

Each subject will complete a Diary Card daily for the 14 days following administration of study medication. The subject will record his/her temperature or have their temperature recorded, twice in the morning (15 minutes apart) soon after getting up and twice at bedtime (15 minutes apart), as well as recording all adverse events. Subjects will be instructed that:

- Should their temperature be confirmed as  $\geq 38.5^{\circ}\text{C}$  on both readings, measured 15 minutes apart, or reach  $39.0^{\circ}\text{C}$  or above on any reading, to contact and visit the investigative site as soon as is practical, to have a clinical assessment and initiation of appropriate investigations and therapy.
- Should they feel feverish they should make additional recordings of their temperature and contact the investigative site
- Should they experience any of the following events with moderate or severe intensity they should contact the investigative site and be prepared to make an additional visit:
  - Flushed face
  - Hot, dry skin
  - Low output of urine and/or dark urine
  - Loss of interest in eating
  - Constipation or diarrhoea
  - Vomiting
  - Headache
  - Aching all over
  - Nausea
  - Chills
  - Abdominal pain, cramps or discomfort

- Subjects will also conduct a stool assessment after each bowel movement. The time of passing the stool will be recorded and the stool assessed as 'Normal', 'Soft but in one piece', 'thick liquid', or 'with rice and water'. The observer will also be asked to record if any blood was visible.

## **8 ADVERSE EVENTS**

### **8.1 Definitions**

#### **8.1.1 Adverse Event**

An adverse event (AE) is any untoward medical occurrence in a subject administered a pharmaceutical product and which does not necessarily have to have a causal relationship with this treatment.

An AE can therefore be any unfavourable and unintended sign (including a clinically significant abnormal laboratory finding\*, for example), symptom, or disease temporally associated with the use of a medicinal product, whether or not considered related to the medicinal product. This includes events from the first study related activity after the subject and his/her guardian has signed the informed permission and assent forms. The following should not be recorded as AEs, if recorded at screening:

- Pre-planned procedure, unless the condition for which the procedure was planned has worsened from the first study related activity after the subject and his/her guardian has signed the informed permission and assent forms.
- Pre-existing conditions found as a result of screening procedures (unless they get worse)

\* A 'clinically significant abnormal laboratory' finding is defined as any clinical laboratory abnormality that suggests a disease and/or organ toxicity and is of a severity which requires active management (i.e. more frequent follow-up or diagnostic investigation) or is clinically significantly outside of the normal range.

#### **8.1.2 Serious Adverse Event**

A serious adverse event (SAE) is an experience that, at any dose, results in any of the following outcomes:

- Death
- A life-threatening\* experience
- In-patient hospitalisation or prolongation of existing hospitalisation
- A persistent or significant disability/ incapacity
- A congenital anomaly/ birth defect
- Important medical events that may not result in death, be life-threatening\* or require hospitalisation may be considered a SAE when, based upon appropriate medical judgement, they jeopardise the subject and may require medical or surgical intervention to prevent one of the outcomes listed in this definition.

\* The term life-threatening in the definition of SAE refers to an event in which the subject was at risk of death at the time of the event. It does not refer to an event that hypothetically might have caused death if it was more severe.

Bacteraemia should also be reported to Akos Ltd following the SAE reporting procedure. If the blood culture grows the M01ZH09 vaccine strain or if the cause of the bacteraemia is undetermined Akos Ltd will report the event as a serious, unexpected, related, adverse event.

### **8.1.3 Severity Assessment Definitions**

The Investigator will be asked to evaluate the severity of the AE according to the following scale:

- Mild: Transient or mild discomfort (<48 hours); no medical intervention/therapy required.
- Moderate: Mild to moderate limitation in activity - some assistance may be needed; none or minimal medical intervention/therapy required.
- Severe: Marked limitation in activity, some assistance usually required; medical intervention/therapy required, hospitalisation possible.

### **8.1.4 Relationship to Study Product Assessment Definitions**

The Investigator will be requested to evaluate the relationship between the AE and the study medication according to the following scale:

- Probably: Good reason and sufficient documentation to assume a causal relationship
- Possibly: A causal relationship is conceivable and cannot be dismissed
- Unlikely: The event is most likely related to an aetiology other than the investigational product

### **8.1.5 Outcome Categories and Definitions**

The outcome will be evaluated according to the following scale:

- Recovered: Fully recovered or by medical or surgical treatment the condition has returned to the level observed from the first study related activity after the subject signed the informed permission and assent.
- Stabilised: This outcome should only be used for cancer events and chronic conditions that cannot be normalised by medical or surgical treatment. This term should only be used when the subject has completed the protocol
- Recovered with sequelae
- Not yet recovered
- Fatal
- Unknown

### **8.1.6 Fever Definition**

Fever is defined as an oral temperature of  $\geq 38.5^{\circ}\text{C}$ . Severe fever is defined as an oral temperature of  $\geq 39.5^{\circ}\text{C}$ . All subjects will be asked to take their temperatures twice a day in the morning when they get up and in the evening when they go to bed for the first 14 days post-dosing.

## **8.2 Collection, Recording and Reporting of Adverse Events**

All AEs must be recorded in the subject's CRF and must be monitored until there is either a return to normal or until the condition becomes stable or is resolved.

All SAEs, whether or not they are judged to be related to the study drug, should be reported, by the Investigator, to Akos Ltd, upon learning of the SAE. SAEs must be reported within 24 hours of knowing about the event or, ideally, within 24 hours of the occurrence of the event. The Investigator must complete the Akos Ltd SAE form with as much information as is available at the time of completion and fax the form immediately to the number provided.

Akos Ltd, the Study Monitor, the Medical Monitor, or a representative of Emergent Product Development UK Ltd, may follow up by requesting clarification or additional information on the SAE, from the Investigator.

It is the responsibility of the Sponsor to report serious, unexpected adverse drug reactions (ADRs) to the relevant regulatory authorities and other Investigators as required under ICH, GCP and relevant regulatory reporting requirements.

It is the responsibility of the Investigator (with the assistance of Emergent Product Development UK Ltd) to report any serious, unexpected ADRs to the Ethics Committee in accordance with ICH guidelines and local requirements.

## **8.3 Follow-up of Adverse Events**

Events discovered or spontaneously reported to the Investigator within 28 days of taking the medication will be documented in the CRF. All SAEs must be followed until all queries related to these AEs have been resolved.

All other AEs must be followed until the Day 28 visit.

The Investigator must forward follow-up information on SAEs to Akos Ltd within 5 days of obtaining the follow-up information. Only changed or new information should be supplied.

## **8.4 Safety Committee**

A safety committee will not be required for this study.

## **8.5 Pregnancy**

Pregnancy is not an AE but the outcome may be. Study subjects must notify the Investigator immediately if they become pregnant. Subjects who become pregnant will be followed up to determine the outcome of the pregnancy. The Investigator will be required to inform Emergent Product Development UK Ltd of a subject's pregnancy and the estimated date of delivery.

Emergent Product Development UK Ltd will follow up with the Investigator around the estimated time of delivery to determine the outcome of the pregnancy.

## **8.6 Overdose**

Overdose is unlikely, as subjects will receive only one dose of study medication and under the supervision of research staff. If a subject accidentally receives more than one dose of study medication, the subject will be observed and treated with antibiotics only if they shed beyond 7 days, develop clinical signs and symptoms of a bacteraemia, develop a persistent silent bacteraemia or become a chronic carrier.

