## 2.4 Clinical Summary

### Summary of Clinical Data to Date

To date *S. typhi* (Ty2 *aroC* *ssaV*) ZH9 has been administered to over 100 healthy adult volunteers in four studies. In the first study (Study MS01.01) 9 subjects (3 per cohort) received doses of either, 10^7, 10^8 or 10^9 CFU of a frozen formulation of the vaccine. In the second study (Study MS01.03) 48 subjects (16 per cohort) received doses of 5 x 10^7, 5 x 10^8 or 5 x 10^9 CFU of a freeze-dried formulation of the *S. typhi* (Ty2 *aroC* *ssaV*) ZH9 vaccine. In the third study (Study MS01.04) 32 subjects received one dose of 5 x 10^9 CFU of the freeze-dried formulation and in the fourth study (MS01.07) a further 16 subjects received one dose of 5 x 10^9 CFU of the freeze-dried formulation. These studies indicate that the vaccine is immunogenic with a good safety profile.

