## 2.7 Risks and Benefits

The anticipated risks of the study are in line with the side effect profile seen to date with M01ZH09. The most likely adverse effects are flatulence, abdominal cramps/discomfort, loose/unformed

stools, headache, nausea, vomiting, chills/rigors, minor elevations in body temperature (up to 38°C) and mild muscle and joint pain in subjects receiving the active vaccine.

For subjects receiving the active vaccine there is a theoretical risk of developing a mild typhoid-like condition. Theoretically there is also a potential risk of subjects developing a clinically significant bacteraemia, or becoming a carrier of the *Salmonella* strain *S. typhi* (Ty2 aroC ssaV) ZH9, and while these outcomes are considered highly unlikely and have not been seen to date in the populations studied, both these conditions would require treatment with antibiotics (refer to Section 6.6 for recommended antibiotic treatment).

There is a potential risk of subjects developing allergic symptoms, such as rashes or anaphylaxis. There may also be other as yet unforeseen risks.

The investigational product will be administered in a bicarbonate solution containing 1.75% (w/v) sodium bicarbonate, 1.1% (w/v) ascorbic acid and 0.02% (w/v) aspartame. Subjects aged 5 to 10 years will receive the vaccine or placebo in 75 mL of bicarbonate solution. Subjects aged 11 to 14 years will receive the vaccine or placebo in 150 mL of bicarbonate solution. The solution is prepared from effervescent bicarbonate tablets using drinking water. The bicarbonate solution may induce some abdominal discomfort and/or cramping around the time of dosing.

Subjects who have received  $5 \times 10^9$  CFU of M01ZH09 have developed an immune response. At present it is not known if the immune response generated by M01ZH09 is protective against infection from *S. typhi*. There can be no assumed benefit for the subjects receiving M01ZH09 even if an immune response is detected; such a response cannot be assumed to be protective. If any protection is obtained, the duration of any such protection is currently unknown.

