## **6.6 Concomitant Medication**

The use of all medication including ‘over the counter’ and herbal products taken in the 4 weeks prior to screening and during the course of the study, up to Day 28, must be detailed in the case report form (CRF). Subjects are to try to avoid all antibiotic/antibacterial use for 14 days before and after dosing. Should a subject require antibiotics he/she must inform the Investigator and may be withdrawn from the study depending on the timing in relation to the vaccination or have their data excluded from the PP analysis. Subjects must not receive any vaccine other than M01ZH09 during the four weeks, post dose, of the study.

Oral contraception is allowed under the protocol. However, should a female subject using oral contraception develop diarrhoea or require antibiotic therapy she will be requested to use additional barrier methods of contraception in combination with a spermicidal preparation.

If a subject has

- a single positive blood culture, or
- a positive stool culture for *S. typhi* at any time after Day 7

he/she must be treated with antibiotics. The first line antibiotic will be ciprofloxacin 20 mg/kg twice daily, taken orally for 10 days. The second line antibiotic will be azithromycin. The dose of azithromycin is dependent upon the age of the subject. Subjects aged 5 to 7 years should receive 5 mL (200 mg) orally once daily for 7 days, subjects aged 8 to 11 years should receive 7.5 mL (300 mg) orally once daily for 7 days and subjects 11 to 14 years should receive 10 mL (400 mg) orally once daily for 7 days. The third line antibiotic is trimethoprim 40 mg/sulfamethoxazole 200 mg per 5 mL of suspension twice daily, 10 mL taken orally for 10 days. In all cases antibiotic therapy will be initiated as soon as the culture results are known.

Any subject who returns for unscheduled visits after Day 14 and has positive blood or stool cultures for *S. typhi* will be treated as a potential carrier and treated with antibiotics and followed up until the infection is clear. Antibiotics will be administered as outlined above at the discretion of the Investigator. The duration of treatment may be up to 28 days to ensure the infection is clear.

The vaccine strain has been shown to be sensitive to ciprofloxacin, azithromycin and trimethoprim/sulphamethoxazole. Ciprofloxacin has been shown to be the treatment of choice for chronic carriers of wild type *S. typhi*.

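### Section 8.6 leaves out the single-positive-blood-culture trigger that Section 6.6 makes mandatory, so the two give opposite antibiotic instructions in one rare overdose case

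*Protocol*

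**What the plan says.** Protocol Section 6.6 (Concomitant Medication) sets the general rule. It names two findings: "a single positive blood culture, or" a stool culture positive for *S. typhi* after Day 7. On either one "he/she must be treated with antibiotics". On timing it adds: "In all cases antibiotic therapy will be initiated as soon as the culture results are known". Nothing in 6.6 exempts a subject who received an extra dose.

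Protocol Section 8.6 (Overdose) sets the rule for a subject who accidentally receives more than one dose. Such subjects are observed and "treated with antibiotics only if they shed beyond 7 days, develop clinical signs and symptoms of a bacteraemia, develop a persistent silent bacteraemia"; the fourth and last condition is chronic carriage. Section 8.6 does not mention 6.6.

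Protocol Section 2.7 (Risks and Benefits), speaking of clinically significant bacteraemia and of carriage, says that "both these conditions would require treatment with antibiotics (refer to Section 6.6 for recommended antibiotic treatment"). It makes no exception for overdose either.

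**The concern.** The two rules differ in form. Section 6.6 is an obligation that starts at the first positive blood culture. Section 8.6 is a closed list introduced by *only if*, and a single positive blood culture is not on it. A bacteraemia without signs appears there only with the qualifier *persistent*. The protocol defines persistent faecal shedding (after Day 7) but not persistent bacteraemia, so the site cannot tell how many cultures, or what interval, the word demands.

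What is at stake is a treatment instruction for children aged 5 to 14 who may have received a live organism. An investigator holding one positive culture from an over-dosed child should not have to choose between an obligation in one section and a restriction in another.

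**Working it through.** There is no figure to reproduce. The check sets the triggers side by side.

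| Finding in an over-dosed child | Section 6.6 | Section 8.6, read literally |
|---|---|---|
| Stool positive for *S. typhi* after Day 7 | Treat (mandatory) | Treat (shedding beyond 7 days) |
| One positive blood culture, with clinical signs of bacteraemia | Treat (mandatory) | Treat (clinical signs) |
| One positive blood culture, judged free of signs, no late shedding, no carriage | Treat (mandatory, once the result is known) | Not on the list: no antibiotics |
| Silent bacteraemia shown to be persistent | Already required at the first positive culture | Treat |
| Clinical signs of bacteraemia, no culture result | Not a mandatory trigger | Treat |

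Reading the table:

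1. Of the two mandatory triggers in 6.6, 8.6 matches the stool trigger in substance and omits the blood trigger: 1 of 2 is missing.
2. Measured against the mandatory triggers of 6.6, the instructions are opposite only in the third row.
3. In that row 6.6 needs one positive culture. Section 8.6 needs more than one, if *persistent* is taken to mean repeated. That reading is an assumption, since the word is undefined.
4. The last row runs the other way: 8.6 allows treatment on clinical signs without a culture, so in that respect it is broader than 6.6.

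**Can the third row occur?** The Study Schedule (Section 1.1) contains no blood culture. Section 6.8.10 provides for extra visits prompted by fever or listed symptoms, with "biological samples taken for culture if clinically indicated". It makes blood cultures mandatory at a confirmed 39.0°C recorded twice over 48 hours, or at any reading of 39.5°C. Section 7.2.1 lets the investigator order cultures after examination and questioning. Most children with a positive culture would therefore have signs that also satisfy 8.6.

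The remaining route is a child cultured for a non-specific complaint on the enquiry list, such as headache or loss of interest in eating, and then judged not to show clinical signs of bacteraemia. Section 8.6 itself foresees a sign-free case by naming silent bacteraemia.

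**The case against.** The strongest reply is that 8.6 was meant only to say that an extra dose is not in itself a reason for antibiotics, and that 6.6 continues to govern everyone. In support, a fully literal *only if* would also bar antibiotics for an unrelated infection in an over-dosed child, which cannot be intended, since 6.6 foresees that subjects may need antibiotics. That is probably the intent. It does not rescue the wording: the list is closed, it deals expressly with bacteraemia, and it sets a stiffer condition for the silent form. If 8.6 is instead taken as the specific rule that prevails over the general one, the protocol gives no reason for the stiffer condition.

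The second reply, that the case hardly ever arises, stands. Other safeguards also apply whatever the dose. One blood culture positive for an *S. typhi* strain suspends dosing (Section 4.8.1, Table 1), and bacteraemia is reported by the SAE route (Section 8.1.2). Neither of these tells the site whether to treat the child.

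Several stronger readings are tempting and should not be drawn:

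- **That 8.6 is the tighter rule throughout.** It is not; it adds a clinical-signs trigger that needs no culture.
- **That the over-dosed child is always the more exposed one.** This holds only if the extra dose was vaccine. Of 150 subjects, 50 receive placebo, and a second placebo dose adds no exposure to the strain.
- **That 8.6 governs children re-dosed after vomiting within 1 hour.** Section 6.8.2 calls for that repeat dose by plan, whereas 8.6 speaks of accidental receipt.
- **That the adult data bound the risk.** Section 2.4 says the strain "has been administered to over 100 healthy adult volunteers in four studies", of whom 16 + 32 + 16 = 64 received 5 × 10⁹ CFU, and Section 2.7 says the outcomes it discusses "have not been seen to date in the populations studied". A reader might turn zero events in 64 into an upper limit. But Section 2.7 refers to clinically significant bacteraemia, and the disputed event is a silent one. The MS01.04 safety summary, which supplies 32 of the 64, reports no blood-culture result. The protocol also gives no rate of accidental overdose.

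**Conclusion.** The inconsistency is real and narrow. For an over-dosed child with one positive blood culture, judged to have no clinical signs of bacteraemia, no shedding beyond Day 7 and no carriage, Section 6.6 requires antibiotics as soon as the result is known and Section 8.6, read literally, withholds them. If the extra dose was vaccine, that child has a stricter treatment threshold than a child dosed correctly.

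The conclusion rests on taking *only if* at face value and on the absence of any cross-reference or override between the two sections. The case would be very rare because culturing is prompted by fever or symptoms; the document does not support putting a number on it. No endpoint, sample size or analysis is affected. Lowest severity: worth correcting, not urgent.

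**What to change.** Add one sentence to Section 8.6: the mandatory antibiotic criteria of Section 6.6 (one positive blood culture, or a stool culture positive for *S. typhi* after Day 7) apply whatever number of doses was received. Keep the clinical-signs trigger in 8.6 as an additional criterion, so that the broader part of that section is not lost.

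The cost is one sentence in the next amendment, with the ethics approval that any amendment needs under Section 12.2. No procedure is added. The one downside is that an over-dosed child with a contaminated blood culture would receive the 6.6 course (first line: ciprofloxacin 20 mg/kg twice daily for 10 days), as any other subject with such a culture already would.
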